# Effectiveness of smartphone-based ambulatory assessment (SBAA-BD) including a predicting system for upcoming episodes in the long-term treatment of patients with bipolar disorders: study protocol for a randomized controlled single-blind trial

**DOI:** 10.1186/s12888-018-1929-y

**Published:** 2018-10-26

**Keywords:** Bipolar disorder, Ambulatory assessment, Prevention, Early warning signs

## Abstract

**Background:**

The detection of early warning signs is essential in the long-term treatment of bipolar disorders. However, in bipolar patients’ daily life and outpatient treatment the assessment of upcoming state changes faces several difficulties. In this trial, we examine the effectiveness of a smartphone based automated feedback about ambulatory assessed early warning signs in prolonging states of euthymia and therefore preventing hospitalization. This study aims to assess, whether patients experience longer episodes of euthymia, when their treating psychiatrists receive automated feedback about changes in communication and activity. With this additional information an intervention at an earlier stage in the development of mania or depression could be facilitated. We expect that the amount of time will be longer between affective episodes in the intervention group.

**Methods/design:**

The current study is designed as a randomized, multi-center, observer-blind, active-control, parallel group trial within a nationwide research project on the topic of innovative methods for diagnostics, prevention and interventions of bipolar disorders. One hundred and twenty patients with bipolar disorder will be randomly assigned to (1) the experimental group with included automated feedback or (2) the control group without feedback. During the intervention phase, the psychopathologic state of all participants is assessed every four weeks over 18 months. Kaplan-Meier estimators will be used for estimating the survival functions, a Log-Rank test will be used to formally compare time to a new episode across treatment groups. An intention-to-treat analysis will include data from all randomized patients.

**Discussion:**

This article describes the design of a clinical trial investigating the effectiveness of a smartphone-based feedback loop. This feedback loop is meant to elicit early interventions at the detection of warning signs for the prevention of affective episodes in bipolar patients. This approach will hopefully improve the chances of a timely intervention helping patients to keep a balanced mood for longer periods of time. In detail, if our hypothesis can be confirmed, clinical practice treating psychiatrists will be enabled to react quickly when changes are automatically detected. Therefore, outpatients would receive an even more individually tailored treatment concerning time and frequency of doctor’s appointments.

**Trial registration:**

ClinicalTrials.gov: NCT02782910: Title: “Smartphone-based Ambulatory Assessment of Early Warning Signs (BipoLife_A3)”. Registered May 25 2016.

Protocol Amendment Number: 03. Issue Date: 26 March 2018. Author(s): ES.

## Background

Bipolar disorder as an affective illness with chronic features shows a very diverse and often unpredictable course of illness concerning the number, length and frequency of recurrent depressive and (hypo) manic states [1]. This condition causes high costs both from an individual as well as from a societal point of view [2]. Patients with bipolar disorder suffer from marked impairment in everyday social and occupational life, e.g. experiencing a diminished quality of life, often due to lower levels of psychosocial functioning [3, 4]. Furthermore, outpatient and inpatient treatment of affective episodes leads to high health care costs. Necessary reductions of working hours, higher absenteeism or premature pension are common and cause substantial secondary economic costs [5, 6].

Though not yet proven the detection of early warning signs (EWS) is considered to improve the course of bipolar illness [7] but it is mainly the patient’s own responsibility as he or she is usually seen by the treating psychiatrist once every few weeks or even months, especially when euthymic. Mood charting as the common tool for EWS detection has several limitations in clinical practice. Firstly, even if done on a daily basis, mood-charting as retrospective and subjective self-assessment, is generally prone to be affected or biased by heuristics, cognitive impairment and symptoms of an evolving episode [8, 9]. Also, demographic characteristics may interfere with the person’s capacity to precisely report the items of interest [10]. Furthermore, the frequency of recording mood, sleep and medication intake reduces over time as many patients with bipolar disorder get tired of mood charting, especially in long episodes of euthymia. However, as the course of bipolar illness remains highly unpredictable even after long periods of euthymia, the cessation of mood charting may turn out to be detrimental [11].

To overcome the outlined problems, ambulatory monitoring has recently been implemented in the long-term treatment of bipolar disorders. This approach is beneficial as it delivers objective, real-time and real-life data in an instant. As a result, much research has been accumulated over the past couple of years employing new technologies [12–18]. Software-based mood charting using the ChronoRecord software is advantageous compared to paper-pencil methods regarding data storage and legibility. This has been validated both for depressive and manic symptoms in bipolar patients [12, 13]. To the best of our knowledge, there are published results of only one clinical trial using smartphones to predict and prevent upcoming episodes. This preliminary single-blind randomized trial studied the impact of electronic self-monitoring of subjective and objective symptoms of bipolar disorders on changes in affective symptoms (primary outcome) as well as depressive and manic symptoms. It was initiated in September 2011 and is referred to as the MONARCA trial [14]. According to reported results of the MONARCA trial electronic self-monitoring, via smartphone, had no significant effect on bipolar symptomatology. For patients in the intervention group there was even a trend of more sustained depressive symptoms [19]. In a second trial the researchers aimed to investigate the usefulness of automated feedback on objective and subjective smartphone data for the reduction of affective symptoms [20]. These results have not yet been published.

Our clinical trial is the first one in German speaking countries to investigate the usefulness of a smartphone-based feedback loop triggering early interventions at the detection of warning signs for the prevention of severe depressive and manic states in bipolar patients. The objective of this randomized controlled trial, referred to as the SBAA-BD study, is to assess the effectiveness of automated feedback about continuous smartphone based ambulatory monitoring of potential early warning signs of upcoming depressive/(hypo) manic episodes. The study investigates whether time to new affective episodes and following hospitalizations can be prolonged in the intervention group. In the MONARCA I trial the placebo group were given a cell phone without an application to monitor the symptoms of interest. However, the knowledge of being continuously monitored for early warning signs may have an impact on the outcome(s) in mood disorders [21]. For this reason we decided to monitor early warning signs in the control group in an identical fashion, by smartphone-based ambulatory assessment including real-time data capture (SBAA). Patients are informed about the group that they are assigned to. Therefore within the 18 months intervention phase identical ambulatory monitoring of EWS of a depressive or (hypo) manic episode is taking place in the control group, serving as a comparator. However the treating psychiatrist has no insight in potential deviations of the patients’ smartphone data from his or her individually calculated baseline data. Irrespective of group assignment, all patients receive guideline-based, state-of-the-art maintenance treatment. In comparison to the MONARCA I trial, the parameters assessed in our study originate exclusively from objective data captured in real time. No event- or time-triggered subjective data like mood or energy level have to be entered by the participants so that the probability of subjective and retrospective biases is expected to be reduced and adherence to study protocol might be enhanced. Additionally, the possibility of worsening depressive symptoms could be reduced as patients do not have to enter their subsequent depressive symptoms every day and process their current mental state in a negative manner [19]. Additionally, patients in this trial stay enrolled for a longer period of time (18 months) than in most of the trials mentioned above. Additionally, we are pursuing a larger sample with 120 randomized patients to overcome limitations of previous work on smartphone-based objective monitoring in bipolar disorder [22]. All data is automatically recorded at the very moment when the behavior (communication and activity) occurred without driving the patients’ attention to the fact that his or her behavior is currently monitored.

We hypothesize that the length of time to a new affective episode and subsequently necessary hospitalization is significantly longer in the Smartphone-Based Ambulatory Assessment group (SBAA+). In this condition clinicians receive automated feedback about substantial change from baseline concerning their patients’ objective smartphone usage data (communication and activity patterns). As a consequence they can intervene at an earlier stage in the development of mania or depression, compared to the Smartphone-Based Ambulatory Assessment group, excluding personalized real-time data-driven therapeutic interventions (SBAA).

## Methods/design

### Design and study setting

This study is a randomized, multi-center, rater-blinded, active-control, parallel group trial within a nationwide research project on the topic of innovative methods for diagnostics, prevention and interventions of bipolar disorders [23, 24]. Assessments are scheduled weekly in the prerandomization phase (4–20 weeks) and monthly in the intervention phase (72 weeks). End of intervention phase is followed by a post-intervention visit after four weeks. Five outpatient centers of psychiatric clinics at German university hospitals (Dresden, Berlin, Hamburg-Eppendorf, Frankfurt, Bochum), specialized in the treatment of bipolar disorders will assess data for this trial. Recruitment shortages are planned to be overcome by opening further study sites (Neuruppin, München, Tübingen). The coordinating site is the University Medical Center in Dresden, supported by the Coordination Center for Clinical Trials (KKS). The clinical trial conforms to the requirements of the MDR (Medical Device Regulation).

### Participants

Potentially eligible participants will be approached at the participating university hospitals (outpatient clinic, inpatient units, and day clinic) by their treating psychiatrists. Furthermore, our study project was presented in local print media. In addition, potential participants could find relevant information on the trials homepage [24]. Finally, board certified psychiatrists were provided with the necessary information by mail as well as in the context of continued medical education training at our hospital. Eligible participants for this trial meet diagnostic criteria for Bipolar Disorders I or II and they can be either symptomatic or asymptomatic at time of enrollment (DSM-5: 296.4×; 296.5×; 296.89). At time of randomization, participants have to be remitted (DSM-5: 296.45, 296.46; 296.55, 296.56; 296.89). Further inclusion criteria consist of (1) age > 18 years, (2) signed informed consent prior to enrollment, (3) ≥ 3 affective episodes in last 5 years, one of them being a (hypo) manic episode, (4) smartphone usage, (5) and each patient must have a sufficient level of understanding to agree to all tasks required by the protocol. Exclusion criteria are comprised of (1) participation in another clinical intervention trial for the last 4 weeks prior to enrollment, (2) substance or other disorders that prevent the patient to understand the nature and consequences of the clinical trial, (3) signs that the patient will probably not comply with the study protocol (e.g. lack of cooperativeness), (4) current substance use disorder (except for tobacco and caffeine), moderate or severe, at enrollment, (5) borderline personality disorder, antisocial personality disorder, (6) dementia, organic brain disorders, (7) patients with a physical illness that probably requires inpatient treatment for more than 4 weeks per annum (exclusion: bipolar disorder), (8) patients working in a shift system which does not ensure regular night sleep, (9) relatives or persons in relation of dependence to study personnel, (10) women of childbearing age, excluding women meeting the following criteria: post-menopausal, postoperative (6 weeks after ovariectomy), regular and correct use of a contraceptive method, sexual abstinence or vasectomy of partner, (11) pregnancy or nursing.

The study population of aim, who meet our criteria, is representative of bipolar patients in outpatient treatment. Pregnant and nursing women as well as women who might get pregnant during the trial are excluded as a requirement for trials conforming to the Medical Device Regulation (MDR).

### Intervention

All patients included in this study use a smartphone with an installed application called movisensXS. MovisensXS is an electronic e-diary software, which additionally can track and transmit smartphone data collected from sensors inside the device. Patients can decide, whether they want to use the study smartphone (a currently available mid-priced Samsung smartphone) or install the app via Google Play Store on their own device. Technical requirements include Android version 4.0 or higher, CPU of 600 MHz or above, acceleration sensor and GPS. In this study, the movisensXS app monitors current location via GPS, an estimate of the covered steps (using the devices’ acceleration sensor), mobile communication parameters (number and duration of incoming and outgoing calls, number and length of incoming and outgoing text messages, number of different call and text contacts), usage duration of common communication apps (e.g. WhatsApp, Facebook Messenger), number and duration of times the display of the device is on/off, as well as rates of transmitted and received data. For enrolled patients, a pseudonymized electronic file is created on the movisensXS platform and all data is transmitted daily to a secured server. Data protection requirements are complied with at any stage of data storage and transmission processes. Every 24 h data are drawn from the data storage server by a feedback server via a secure connection and data of patients in the intervention group are compared with individual baseline data performed. The intervention-algorithm is based on a combination of threshold values associated with parameters which are linked to DSM-5 criteria of bipolar disorders, i.e. change in goal-directed or non-goal directed activity and change of communication pattern (e.g. more talkative than usual). Psychomotor agitation/retardation is operationalized by movement patterns derived from two smartphone sensor systems. Daily travel distances in kilometers per day are calculated via GPS coordinates. The acceleration sensor in the smartphone tracks acceleration in three spaces. Daily movement activity is assessed by number of steps. General inactivity is calculated by numbers of hours without any smartphone activity, which includes no acceleration data, no phone calls or text messages and the smartphones display being turned off. Communication is operationalized by tracking the frequency and length of phone calls and text messages using the smartphone.

First, daily values are calculated for all monitored parameters. During a stabilization period (four weeks of euthymia) in the prerandomization phase individual baseline values (mean and standard deviation) for the persons’ typical smartphone usage, communication and activity behavior in the following eight parameters are calculated: (1) travelled distance (km/day), (2) steps/day, (3) number of outgoing calls/day, (4) average phone call duration/day, (5) length of outgoing text messages/day, (6) hours when smartphone is inactive, (7) frequency of display on/day and (8) duration of display on/day. During the intervention phase daily deviations of daily values from baseline are calculated. A defined alarm threshold is exceeded when two or more parameters exceed or fall below the 20% or above the 80% percentile on three subsequent days. The direction of the deviation has to be the same for each variable on these three days but can differ between different variables. For patients in the intervention group, alarms are automatically forwarded by email to the respective study center. The attending psychiatrist contacts the patient and decides whether an affective episode is present or developing and carries out the next standard procedures as in usual practice, e.g. appointing a personal contact to discuss treatment options with the patient. If no affective episode is present and the alarm is not explicable by current external circumstances of the patients’ situation the signal is rated as a false alarm. In this case, the alarm thresholds are raised by 5% (values of the 20% and the 80% percentile). In case of an undetected mood episode during the intervention phase the thresholds will be lowered by 10%. Information flow is depicted in Fig. 1.

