#### Outcomes

Primary outcome of this trial is time to new affective episode, defined by DSM-5 criteria for depressive, manic or hypomanic episode. The primary outcome will be determined by SCID I section A (for DSM-IV, additional DSM-5 question for energy/activity being included), criteria for current depressive and (hypo) manic episode, in monthly assessments during the intervention phase. The primary outcome is clinically highly relevant to determine the affective and mental stability of bipolar patients.

Secondary endpoints are (1) time to a new depressive episode, (2) time to a new (hypo) manic episode, (3) time to a new affective episode defined by DSM-5 but with modified time criterion of ≥ four days of episode duration, (4) percentage of assessments during intervention phase at which the original DSM-5 criteria for an affective episode are met, (5) percentage of assessments during intervention phase at which the modified DSM-5 criteria for an affective episode are met. These outcomes will also be determined by SCID I section A (for DSM-IV, additional DSM-5 question for energy/activity being included), criteria for current depressive and (hypo) manic episode, in monthly assessments during the intervention phase. Further secondary outcomes are (6) percentage of assessments during intervention phase at which criteria for an affective episode, defined by YMRS (> 12) and IDS-30 (> 18) score are met and (7) average severity of manic and depressive symptoms at assessments during intervention phase. These criteria are estimated by total YMRS and IDS-C30 scores at every assessment. Operationalization of the secondary outcomes (8) percentage of assessments during intervention phase at which the patient was hospitalized for an affective episode, and (9) percentage of days during intervention phase at which the patient was hospitalized for an affective episode, is self-explanatory. (10) Number of adverse events is measured by the SAE (serious adverse event) reporting form included in the electronic case report form (eCRF).

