### Randomization and blinding

A randomization list is stored in the electronic database where all collected data is entered using eCRFs. Based on this list, patients are allocated to the two groups (SBAA resp. SBAA+) by block randomization, stratified by age and type of bipolar disorder (I or II) for every study site. Pseudonymized files are created in the database for enrolled patients. The system allocates patients to the groups corresponding to the stored algorithm for randomization and the required stratification factors. The patient and the assigned psychiatrist are automatically and instantly informed about which group (SBAA vs. SBAA+) the patient was allocated to once randomization is carried out via the database system. As regular ratings must not be biased by group allocation knowledge, the observer/rater remains blinded. Both treating psychiatrist and patient are asked explicitly not to disclose any information allowing conclusions regarding group allocation. As the study psychiatrists are not blinded, there was no need to provide special procedures for emergency unblinding.

The intervention phase is planned for 18 months (72 weeks). During this time, state-of-the-art treatment of the bipolar condition continues for both groups. Attending psychiatrists will receive automatic feedback from the movisensXS feedback server, every time the previously calculated individual thresholds of patients in the SBAA+ group are significantly exceeded in any direction. A standardized procedure follows, where the psychiatrist contacts the patient to assess, whether (a) the changes in smartphone usage patterns can be explained by external circumstances, or (b) show no hint for the beginning of a new affective episode (false alarm), or (c) the changes result from early signs of bipolar episodes. In this case treatment options are discussed with the patient as in regular guideline-based treatment. Additionally, in the case that the rater detects an affective episode, the study clinician will be informed so that thresholds can be changed towards more sensitivity if the patient is enrolled in the intervention group and no automatic alarm has been present.

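### Minor: as worded, the alarm-threshold adjustment moves the lower (20% percentile) limit the wrong way after a false alarm and after a missed episode

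*Protocol article*

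**What the plan says.** The Intervention section of the protocol article builds an individual baseline (mean and standard deviation) for eight smartphone parameters during four euthymic weeks. It then states: "During the intervention phase daily deviations of daily values from baseline are calculated". An alarm threshold counts as exceeded "when two or more parameters exceed or fall below the 20% or above the 80% percentile on three subsequent days". Each parameter therefore has a lower and an upper limit.

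Two adjustments follow. When the psychiatrist finds no episode and no external explanation: "In this case, the alarm thresholds are raised by 5% (values of the 20% and the 80% percentile". When an episode was missed: "In case of an undetected mood episode during the intervention phase the thresholds will be lowered by 10" (per cent).

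The Randomization and blinding section describes what sets off the second step: "in the case that the rater detects an affective episode, the study clinician will be informed". It then gives the purpose, on condition that the system itself had raised no alarm: "so that thresholds can be changed towards more sensitivity if the patient is enrolled in the intervention group". The same section says that feedback is sent when thresholds are exceeded in either direction.

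**The concern.** One verb is applied to both limits, and the parenthesis names both percentile values. For an upper limit, up means stricter and down means more sensitive. For a lower limit it is the reverse: a higher limit is easier to fall below and a lower one is harder. Followed exactly, the rule loosens the lower limit just after an alarm was judged false. It tightens that limit just after an episode was missed, against the stated aim.

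Forwarding these alarms to the psychiatrist is what separates SBAA+ from SBAA, so the rule describes the intervention itself. Low values of steps, distance and outgoing calls are caught by the lower limit.

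The two steps differ in what they can reach:

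- The false-alarm step can operate before a patient's first episode. A psychiatrist still screens each alarm.
- The missed-episode step is set off by an episode that the blinded rater detects. The Outcomes section says: "Primary outcome of this trial is time to new affective episode, defined by DSM-5 criteria for depressive, manic or hypomanic episode". If the detected episode meets those criteria, that patient's primary event has already happened. The step can then bear only on later detection and on secondary outcomes, such as the "percentage of assessments during intervention phase at which the original DSM-5 criteria for an affective episode are met".

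**Working it through.** The article gives no alarm rate, so there is no stated figure to reproduce. The check is whether the direction depends on how the percentages are read.

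**Inputs from the article (Intervention):** limits at the 20% and 80% percentiles; +5% after a false alarm; -10% after a missed episode; at least two of eight parameters on three successive days, each parameter keeping its direction.

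**Assumptions not in the article:** stable euthymia, roughly normal daily values, and independent days and parameters. For the value reading, the coefficient of variation (CV) is 0.3, 0.5 or 1.0.

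**Step 1: daily tail probabilities.** The start is 20% in each tail, with z(0.80) = 0.8416.

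- *Percentile points:* 20 + 5 = 25 and 80 + 5 = 85; 20 - 10 = 10 and 80 - 10 = 70.
- *Relative change of rank:* 20 × 1.05 = 21 and 80 × 1.05 = 84; 20 × 0.90 = 18 and 80 × 0.90 = 72.
- *Raw percentile value, mean set to 1:* the limits 1 ± 0.8416 × CV are multiplied by 1.05 or 0.90. Example, CV 0.5: the lower limit 0.579 becomes 0.608, and Φ((0.608 - 1)/0.5) = 0.217.
- *Deviation from the mean, scaled in size:* 0.8416 × 1.05 = 0.884 gives 0.188; 0.8416 × 0.90 = 0.757 gives 0.224.

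| Reading | Lower tail after false alarm / miss | Upper tail after false alarm / miss |
|---|---|---|
| Percentile points | 25% / 10% | 15% / 30% |
| Relative rank | 21% / 18% | 16% / 28% |
| Raw value, CV 0.3 | 23.7% / 13.8% | 14.7% / 33.6% |
| Raw value, CV 0.5 | 21.7% / 16.9% | 16.3% / 28.9% |
| Raw value, CV 1.0 | 20.2% / 19.6% | 17.5% / 25.5% |
| Deviation, scaled in size | 18.8% / 22.4% | 18.8% / 22.4% |

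The upper tail moves correctly in every row. The lower tail moves the wrong way in the first five rows and the right way only in the last. The direction in those five rows does not depend on independence. The value reading needs a positive lower limit, which under normality means CV below 1/0.8416 = 1.19.

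**Step 2: three-day lower-tail run for one parameter,** (daily probability)³. The start is 0.20³ = 0.80%. After a false alarm / a miss:

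- percentile points: 0.25³ = 1.56% / 0.10³ = 0.10%
- relative rank: 0.93% / 0.58%
- raw value, CV 0.3, 0.5, 1.0: 1.33%, 1.02%, 0.83% / 0.26%, 0.48%, 0.75%
- scaled deviation: 0.67% / 1.13%

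**Step 3: total alarms.** Let q = p_low³ + p_high³. The alarm probability in a given three-day window is 1 - (1 - q)⁸ - 8q(1 - q)⁷. At the start q = 0.016, which gives 0.0067.

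| Reading | After false alarm | After miss |
|---|---|---|
| Percentile points | 0.0094 | 0.0196 |
| Relative rank | 0.0047 | 0.0193 |
| Raw value, CV 0.3 | 0.0071 | 0.039 |
| Raw value, CV 0.5 | 0.0055 | 0.021 |
| Raw value, CV 1.0 | 0.0049 | 0.015 |

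Under every literal reading total alarms rise after a miss, because the upper tail gains more than the lower tail loses. After a false alarm they fall in three rows, rise slightly in one (CV 0.3) and rise clearly only with percentile points.

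**The case against.** The best defence is that the section uses *threshold* without a direction. It counts falling below the 20% percentile as one way of exceeding the threshold, so *raised* can mean harder to exceed and *lowered* easier. That agrees with the aim of more sensitivity after a miss and with thresholds that can be exceeded either way. The section also works with deviations from a baseline mean and standard deviation. A limit on that scale is signed, and enlarging it by 5% moves the lower limit outward. This is the last row of the first table, and it is right for both tails. A journal article may also leave the exact parametrisation to a software specification.

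Much of this stands. It makes the outward and inward movement the very likely intention, and it keeps the point minor. It does not remove the point: the parenthesis says that the values of both percentiles are raised, and nothing says that the two limits move in opposite directions or that the percentage scales a distance from the mean. The article did not leave the rule out. It states the rule with its numbers, in words that misdirect one limit if followed.

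Three stronger inferences are tempting, and the document supports none of them:

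- *The server is miscoded.* The article does not show the code.
- *The alarm system as a whole becomes less sensitive after a miss.* Step 3 shows total alarms rising in every literal reading. The fault is confined to the lower tail, and that tail is not the only route to reduced activity: hours of smartphone inactivity would go up and meet the upper limit.
- *The trial's power or primary analysis is compromised.* Neither the sample size inputs nor the log-rank comparison uses the threshold rule.

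**Conclusion.** The point holds as a minor wording error. Applied to the percentile values as written, the adjustment is right for the upper limit and backwards for the lower one, and for that limit it contradicts the article's own aim after a missed episode. The direction is the same whether the percentages mean points, relative ranks or positive raw values. It is right only if *raised* means stricter or if the percentages scale a deviation from the mean.

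The size is uncertain. The parenthesis speaks of values, so the raw-value rows fit it better than the larger percentile-point figures, and those rows rest on an assumed CV and normality. The three-day and total-alarm figures also assume independence. If the server already moves the limits correctly, what remains is a published rule that misdescribes the intervention and could mislead anyone who replicates it.

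**What to change.** Replace the two adjustment sentences with: after a false alarm both limits move away from the baseline mean (lower limit down, upper limit up); after an undetected episode both move towards it (lower limit up, upper limit down). In the same edit, say whether 5% and 10% are percentile points, relative changes of the value, or changes in distance from the mean.

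Confirm once that the feedback server does this, and correct it if not. The cost is two sentences and one look at the code, with a short software correction only if the literal rule was programmed. No patients or visits are added.
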